## Methods and design

### Study design

This is a non-randomised, delayed intervention study design. The study is not randomised since the educational intervention will be administered in groups and randomising groups will require unrealistic sample size. However, using repeated measures and a delayed intervention design provides an optimal solution without compromising the study quality. Such a design is preferable for evaluation of the educational intervention since all participants receive the intervention and the design enables measure of progress across and within groups, including control for possible (although unlikely) differences between groups at the starting time.

Clinicians participating in this study will be recruited from a population of general practice registrars who are undergoing GPTerm1 or GPTerm2 stages of training at GP Synergy (a major provider of general practice training in Australia), at two training sites. Participants from site A will be the ‘early intervention group’ while the group at site B will be the ‘delayed intervention group’. The two interventions will be identical and will differ only by the time of implementation. Participants will undergo evaluations of clinical reasoning (based on the Script Concordance Test (SCT) [15] upon commencement of project (Time Point 1: before the early intervention), immediately after the early intervention and before the delayed intervention starts (Time Point 2), and at the end of the delayed intervention (Time Point 3).

The impact of the intervention will be measured by comparing the progress each group makes (changes in SCT scores) over each intervention period.

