### Sample size

Two systematic reviews suggest that the effect size on SCT between resident doctors and expert doctors ranged 0–3.2; typically around 1 and the effect of educational interventions such as Educational meetings/interactive educational sessions was d > 1 [16,17]. Based on those studies, we expect that the intervention will yield an effect size of d ≥ 1.0 measured by the differences in the SCT results between the intervention and the control groups between Time Point 1 and Time Point 2. A similar increase is expected for the delayed intervention group between Time Point 2 and Time Point 3. Therefore, a sample size of 34 clinicians (17 intervention & 17 control) will have 80% power to detect an effect size of d = 1 (one sd.) with an alpha of 0.05 (two sides) [18].

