### Statistical analysis

The main analyses in this study will employ Analysis of Variance (ANOVA). (a) Factorial ANOVA will be used to compare the two groups at Time Point 1 and identify possible differences on SCT scores across groups; (b) One-way repeated measure ANOVA will be used to measure the impact of the intervention by comparing differences in SCT scores within individuals and across groups between Time Point 1–2 and between Time Point 2–3. This analysis is appropriate as it allows identifying the source for the change in the SCT scores (intervention, initial level of competence or errors [20], and testing the hypothesis that the change in the SCT was made by the intervention. We set up a significance level of p < .05 to demonstrate that the intervention was successful.

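### The success criterion of p < .05 is not tied to the one contrast the study was sized on, so its false-positive rate is undetermined

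*Protocol article*

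**What the plan says.** Three sections of the protocol article bear on this.

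- **Study design.** Two non-randomised groups take the Script Concordance Test (SCT) at three time points. Impact is measured by "comparing the progress each group makes (changes in SCT scores) over each intervention period". There are two such periods, and neither is ranked above the other.
- **Sample size.** The effect of d = 1 is defined on "differences in the SCT results between the intervention and the control groups between Time Point 1 and Time Point 2". For this contrast, 17 per group is said to give 80% power at a two-sided alpha of 0.05. The section adds: "A similar increase is expected for the delayed intervention group between Time Point 2 and Time Point 3". It does not say whether that second increase is required for success, supports it, or could establish it alone.
- **Statistical analysis.** Part (a) is a baseline check: "Factorial ANOVA will be used to compare the two groups at Time Point 1". Part (b), a one-way repeated-measures ANOVA, assesses impact by "comparing differences in SCT scores within individuals and across groups between Time Point 1–2 and between Time Point 2–3". The section closes with the decision rule: "We set up a significance level of p < .05 to demonstrate that the intervention was successful".

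The decision rule names no test, does not say whether one or all must pass, and does not refer back to the contrast in the Sample size section.

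**The concern.** A threshold of 0.05 controls error at 0.05 only when it is attached to one identified test, or to several with a stated rule for combining them. Here the threshold follows a list of comparisons. If the choice among them stays open until the results are known, the stated 0.05 is not the error rate of the claim that GET succeeded.

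The type of comparison matters too. In standard usage a one-way repeated-measures ANOVA has time as its only factor and contains no group-by-time term. Read literally, a significant change within individuals could decide success. Participants sit the SCT three times while in training, so such a change can include retest gain and ordinary learning. The delayed group is there to separate these from an effect of GET. A rule that does not require the between-group contrast gives up that protection.

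**Working it through.** **1. Reproduce the plan's figure.** Inputs from the Sample size section: d = 1, two-sided alpha 0.05, power 80%, 1:1 allocation.

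- Normal approximation: n per group = 2(1.96 + 0.84)² / 1² = 15.7, so 16.
- Two-sample t-test: 16.7, so 17 per group and 34 in total. Power at 17 per group is 80.7%.

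The stated 34 is reproduced as the size for one two-group comparison at 0.05.

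**2. Count the candidate tests.** The baseline comparison in part (a) is not a test of success and is left out. Part (b) can be read as two between-group tests (early versus delayed change, Time Points 1–2 and 2–3), or as those two plus the within-group change in each group over its own intervention period, making four.

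**3. Error rate if the tests were independent.** 1 − 0.95^k gives 9.75% for k = 2 and 18.5% for k = 4.

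**4. Allow for correlation.** The tests share data. Assume equal variances and a common correlation r between any two of the three scores; the documents give no r. Each change score then has variance 2(1 − r), and successive changes have covariance −(1 − r). Their correlation is −0.5 whatever r is, which is why r hardly matters when there is no practice gain. Simulation with 17 per group, no GET effect, no practice gain, and r from 0.3 to 0.7 gives:

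| Rule for success | p < .05, either direction | Only results favouring GET |
|---|---|---|
| Sized contrast alone | 5% | 2.5% |
| Both between-group tests | 0.8–0.9% | 0.4–0.5% |
| Either between-group test | about 9% | about 4.5% |
| Any of the four | about 15% | about 7.6% |

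**5. Add a practice gain.** Assume every participant gains 0.3 SD per interval and GET does nothing. Both the gain and r are assumptions. For a within-group test, the gain in units of the SD of change is 0.3 / √(2(1 − r)):

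- r = 0.3: 0.3 / √1.4 = 0.25
- r = 0.6: 0.3 / √0.8 = 0.34

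The any-of-four rule then yields p < .05 in about 35% of trials at r = 0.3 and about 49% at r = 0.6. With a gain of 0.2 SD and r = 0.5 it is about 28%. The either-between-group rate stays at about 9% throughout, because a gain common to both groups cancels. The excess therefore comes from the uncontrolled within-group tests and is not a multiplicity effect.

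**6. Compare the remedies.**

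- Naming the sized contrast alone keeps alpha at 5%, power at 80.7% and N at 34.
- Letting either between-group test succeed, with alpha split to 0.025 each, cuts power per test at 17 per group to 71%. Restoring 80% needs 20.3, so 21 per group and 42 in total.

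**The case against.** The text states no any-of-four rule. It sets a single significance level and speaks of one hypothesis. The phrase about individuals and groups may simply describe the within- and between-subject parts of one repeated-measures model per period. The Study design section compares the progress of the groups, which points to a between-group test. The Sample size section comes close to identifying the deciding contrast. A full protocol or analysis plan, not shown, may settle the matter.

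Much of this stands. A reader might infer that the chance of falsely declaring GET successful is well above 5%. The documents do not support that as a fact, because it holds only under a rule they do not state. Even under the either-between-group rule, the chance of a false result in favour of GET is about 4.5%; that exceeds the 2.5% for one test but is not above 5%. Nor do the 35–49% figures measure multiplicity: they depend on an assumed practice gain and on counting within-group tests as decisive.

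The gap itself remains. The article chose to state a success criterion, and the criterion as stated does not identify a test. That is a rule fixed loosely, not a detail left to another document. The Sample size section never calls its contrast primary, and the Statistical analysis section does not refer to it.

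**Conclusion.** The point holds as a defect in how the success rule is anchored. The 0.05 and the 80% power belong to the between-group change over Time Points 1–2, while the success claim rests on a wider set of comparisons. Depending on a choice the text leaves open, the two-sided error rate runs from under 1% to about 15%, and is exactly the intended 5% on one natural reading. It is undetermined, and has not been shown to be inflated.

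The more serious exposure is the within-individual route. If it may decide, success can arise without any GET effect, at a rate set by retest and training gains that the documents do not quantify. All simulated figures assume 17 per group, normal scores and equal correlation between time points. The practice-gain figures further assume the gain. The matter should be corrected, and correcting it is easy.

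**What to change.** Replace the closing sentence of the Statistical analysis section with wording such as: *GET will be judged effective only if the group-by-time contrast over Time Points 1–2 (early minus delayed change in SCT score) is significant at two-sided 0.05 in favour of GET. The Time Point 2–3 comparison and all within-group changes are supportive, will be reported as estimates with 95% confidence intervals, and cannot establish success.* The model in part (b) should be described so that it contains this group-by-time term.

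The contrast is the one already used for the sample size, so N = 34, the 5% alpha and the stated power all stand. The only loss is the option of claiming success from a secondary comparison.

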## Discussion

This project aims to evaluate the effectiveness and feasibility of an innovative clinical educational intervention named the Guideline Enhancement Tool (GET). The study will explore the role of the GET in enhancing clinical reasoning in general, and specifically related to the management of hypertension in general practice. The project focusses on the important area of clinician engagement with clinical practice guidelines, and includes a bi-directional format that can lead to the enhancement of the guidelines.

The project is expected to result in three major outcomes:Enhanced engagement of general practitioners with hypertension guidelinesA validated clinical education strategy that can be used in GP training to enhance the decision-making processes related to the management of hypertension. This has the potential to be adapted to other clinical conditions and training programsRecommendations for enhancing the feasibility and practicality of hypertension guidelines within general practice contexts

As the clinical education strategy aims to enhance clinicians’ clinical reasoning abilities, it has the potential to benefit clinicians in their clinical decision-making across many areas, beyond the focus of this project. The educational strategy also serves as a model to inform the process of future clinical guideline development.

The study design presented in this protocol explores features that relate to the effective use of clinical practice guidelines. The study thus addresses a significant problem in clinical education that can benefit from exploration from a new perspective.

## Abbreviations

GET: Guideline enhancement tool
GP: General practitioner
SCT: Script concordance test
UNSW: University of New South Wales
